### 6.1.2. Background and demographic characteristics

Demographic variables such as race, gender, and other baseline categorical parameters will be analyzed for treatment group comparability using the Chi-square test and Fisher’s exact test. Continuous type of parameters will be analyzed using the t-test and analysis of variance (ANOVA).

### 6.1.3. Study medication

Summary statistics for the total exposure to study drug during the 6-week double blind treatment period (number of doses) will be computed for each treatment group.

### 6.1.4. Concomitant therapy

Concomitant medications will be summarized by therapeutic/pharmacological class and treatment group. In addition, they will be listed by treatment group, name of drug, dates administered and indication.

Use of rescue pain medication will be evaluated as an efficacy parameter.

### 6.1.5. Efficacy evaluation

The primary analysis will be an intent-to-treat analysis. The standard 95% confidence intervals for treatment differences between each dose and placebo groups will be constructed for the primary efficacy endpoint. Since the study is stratified with respect to the SNAP status, separate confidence intervals will be constructed for each stratum. If there is no interaction between treatment efficacy and SNAP, the two intervals will be combined across the strata to have a global confidence interval for evaluating each dose effect. If the safety profiles for the four dose groups are similar, the recommended dose will be the one with the best efficacy (largest lower bound of the confidence interval).

Similar analyses will be repeated for the secondary efficacy endpoints. For the secondary endpoint analyses, the weekly pain scores will be calculated for each subject. In order to take advantage of such repeated measurements in the analysis, a 95% confidence interval of the difference between a dose group and the placebo will be constructed at each week. These intervals will be combined using the technique by Wei and Johnson25 to obtain a single more informative confidence interval for the treatment difference over the entire study period.

Subjects with greater than 0.35-unit pain improvement on the 13-point Gracely scale at Week 6 will be classified as treatment successes. Treatment group comparisons will be carried out using the Chi-square test and Fisher’s exact test. The standard confidence interval of the difference of the weekly success rates between a dose group and placebo will be constructed. For this dichotomized response, a single interval estimate across the entire study period will be computed using the Wei and Johnson technique.

In addition, an analysis of covariance (ANCOVA) which adjusts for the differences in baseline Gracely pain scale will be conducted for both primary and secondary efficacy endpoints. Primary and secondary efficacy analyses will also be repeated adjusting for other factors that may affect the outcome. Candidate predictive factors are SNAP amplitude at baseline, type of sensory neuropathy (DSP versus ATN), CD4 counts, plasma viral load, age, body mass index (BMI), duration of disease, and background antiretroviral therapy.

Additional efficacy analyses will include per protocol analyses. The previously described statistical approach will be repeated for this population.

For those subjects in the prosaptide groups who were treatment successes, the mean Gracely pain scale during the crossover placebo period will be calculated. The time at which the mean Gracely pain scale returns to the baseline level will be summarized by treatment group.

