| **Statistical methods:** | The primary analysis will be an intent-to-treat analysis. The standard 95% confidence intervals for treatment differences between each dose group and placebo will be constructed for the primary efficacy endpoint. If the safety profiles for the dose groups are similar, the recommended dose will be the one with the best efficacy (largest lower bound of the confidence interval). Similar analyses will be repeated for the secondary efficacy endpoints. In addition, an analysis of covariance which adjusts for the differences in baseline Gracely pain levels for the primary efficacy endpoint will be conducted.  A single interim futility analysis will be conducted after the first 200 subjects have completed the 6-week double-blind treatment period. Specifically, an evaluation of the primary efficacy endpoint between each treatment arm and placebo will be assessed. Treatment arms determined to have minimal possibility of efficacy in a futility analysis will be dropped from the study. In addition, an estimate of variance of the primary efficacy endpoint will be performed, and an evaluation of effect of SNAP will be assessed. Subjects will be added if required to a maximum of 500 randomized subjects. |

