### 3.3.2. Treatment assignment

Subjects will be stratified by center and SNAP status and randomized to receive prosaptide 2, 4, 8 or 16 mg or look-alike placebo every 24 hours for 6 weeks. All blocks of 5 kits that have had one or more kits assigned must be used until the supply is exhausted in order to maintain the blind. A mechanism for removing the 2 mg kit from a block with five intact, unassigned study kits will be implemented by the Sponsor in a manner that preserves the blind. All subsequent shipments of study drug will consist of four study kits: 4, 8 or 16 mg prosaptide or placebo. Study kits will be distributed in numerical order, with each subject receiving the next kit for his or her SNAP group available at the site.

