# 6. Statistical methods

## 6.1. Statistical methods

This is a double-blind, randomized, placebo controlled study with five dose groups (0, 2, 4, 8, 16 mg/per day). The primary efficacy endpoint is the change of the Gracely pain average score during Week 6 from the Week 0 baseline level (Week 0 minus Week 6 score). The primary objective is to select at least one dose group which is significantly better than the placebo with respect to this endpoint. Furthermore, the dose response relationship among these four groups will be examined.

Due to the slow enrollment, the protocol is amended to restrict further enrollment in the lowest dose arm (2 mg). It is expected that a sufficient number of subjects will have been treated at 2 mg before the amendment is fully implemented. An inferential statistical comparison between the 2 mg and placebo groups will still be carried out if there is a sufficient statistical power to detect a clinically meaningful treatment difference. Regardless, all dose groups will be used to characterize safety and dose response.

The study will be stratified with respect to SNAP (+ or -). For each stratum, a random treatment allocation rule will be utilized so that the balance among these five dose groups (four dose groups after the amendment) within each center will be maintained during the study.

It is planned that the data from all centers that participate in this protocol will be combined, so that an adequate number of subjects will be available for analysis. The results from each center will also be presented individually. In addition, it is planned that the data from both SNAP positive and SNAP negative subjects will be combined in the final analysis if there is no interaction between treatment effects and SNAP status.

The significance for all statistical tests will be reported at the p=0.05 level, and all tests will be 2-sided. Each dose group will be compared to the placebo group and a 95% confidence interval for each comparison will be provided. Because this is a phase 2 study, no adjustments for multiplicity will be made.

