## Sample size and power considerations

Based on two studies of neuropathic pain in subjects with HIV-SN20, 21, the average placebo response in the Gracely pain scale is about 0.17, and the standard deviation of the change in Gracely pain scale is approximately 0.35. Therefore, any treatment differences of less than 0.17 can be considered to be not clinically meaningful. This study is designed to detect a minimum treatment difference of 0.17 between any dose group and placebo. In order to have at least 80% power to detect this difference and a significance level of 0.05 (2-sided), 70 evaluable subjects at the end of the trial in the 4 mg, 8 mg, 16 mg and placebo groups are required. The power to detect this difference between the 2 mg and placebo groups will also be calculated before the final efficacy analysis. With 70 subjects per group, the 95% confidence interval for the changes between any dose group and the placebo covers (d-0.12, d+0.12), where d is the observed difference between the two groups. Allowing for early dropouts and assuming the enrollment of 45 subjects in the 2 mg group, 355 subjects will need to be enrolled for the final analysis.

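### The primary interval, which also picks the dose, is not adjusted for baseline pain; ranking the planned baseline ANCOVA first would gain precision at almost no cost

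*Protocol*

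**What the plan says.** Section 6.1 defines the primary endpoint as a change score: the Week 0 Gracely average minus the Week 6 average. Section 6.1.5 sets the primary analysis: "The standard 95% confidence intervals for treatment differences between each dose and placebo groups will be constructed for the primary efficacy endpoint". An interval is built in each SNAP stratum and, if treatment and SNAP do not interact, "the two intervals will be combined across the strata to have a global confidence interval for evaluating each dose effect". If the safety profiles are similar, the recommended dose is the one whose interval has the largest lower bound.

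Baseline pain enters later in the same section: "In addition, an analysis of covariance (ANCOVA) which adjusts for the differences in baseline Gracely pain scale will be conducted". The synopsis keeps this order. It first gives the intervals ("The standard 95% confidence intervals for treatment differences between each dose group and placebo will be constructed for the primary efficacy endpoint") and then adds "In addition, an analysis of covariance which adjusts for the differences in baseline Gracely pain levels for the primary efficacy endpoint will be conducted".

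Section 6.3 sizes the trial on the change score: "the standard deviation of the change in Gracely pain scale is approximately 0.35". It does not state a baseline-to-Week 6 correlation, or a residual SD after adjustment for baseline.

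The order of the two analyses is fixed in the protocol itself, so it is not a detail left to a statistical analysis plan.

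**The concern.** Subtracting baseline from Week 6 amounts to assuming that Week 6 pain moves one-for-one with baseline pain. If the true within-group slope is below 1, the change score over-corrects. It then carries noise from baseline that a fitted slope would remove.

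Two things are at stake:

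- **Precision.** The intervals are wider than the same data could give. Width matters here: Section 6.1.8 drops arms on predicted 95% intervals and resizes the trial to hold the interval length within 0.24, and slow enrolment has already led the sponsor to curtail the 2 mg arm.
- **Dose ranking.** A chance baseline difference between two arms shifts their contrast by (1 − slope) times that difference. An imbalance in the placebo arm moves all contrasts together, but imbalances among the active arms can reorder the lower bounds that choose the dose.

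**Working it through.** **Inputs (Section 6.3).** Difference 0.17; SD of change 0.35; two-sided 0.05; at least 80% power; 70 evaluable per group; half-width 0.12.

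**1. Reproduce the plan's figures.**

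- n per group = 2 × [0.35 × (1.960 + 0.842) / 0.17]² = 66.5, so 67. The t-based calculation gives 68. The plan's 70 is slightly above both.
- Power at 70 per group is 82.0% (normal) or 81.4% (t).
- Half-width = 1.96 × 0.35 × √(2/70) = 0.116, which rounds to 0.12.

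The plan meets its own targets with the change-score SD and no baseline adjustment.

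**2. Variance after adjustment.** Let r be the within-group correlation of Week 0 and Week 6 means, and k the Week 6 SD divided by the Week 0 SD.

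- Change-score variance: SD₀² × (1 + k² − 2rk)
- ANCOVA residual variance: SD₀² × k² × (1 − r²)
- Difference: SD₀² × (1 − rk)², where rk is the slope of Week 6 on baseline

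The difference is never negative. Apart from one degree of freedom, ANCOVA cannot be less precise. With equal SDs (k = 1) the variance ratio is (1 + r)/2.

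**3. Equal SDs, change SD held at 0.35, 70 per group (r is assumed).**

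| r | Variance ratio | Residual SD | Power, normal / t | Half-width | n per group for 80% power |
|---|---|---|---|---|---|
| change score | 1 | 0.350 | 82.0% / 81.4% | 0.116 | 67 |
| 0.3 | 0.65 | 0.282 | 94.6% / 94.3% | 0.0935 | 44 |
| 0.5 | 0.75 | 0.303 | 91.3% / 90.9% | 0.1004 | 50 |
| 0.7 | 0.85 | 0.323 | 87.6% / 87.2% | 0.1069 | 57 |
| 0.9 | 0.95 | 0.341 | 83.8% / 83.3% | 0.113 | 64 |

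**4. Unequal SDs (k is also assumed; normal approximation).**

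| k | r | Slope | Variance ratio | Power | Half-width |
|---|---|---|---|---|---|
| 0.8 | 0.5 | 0.40 | 0.571 | 96.7% | 0.0877 |
| 1.2 | 0.5 | 0.60 | 0.871 | 86.8% | 0.1082 |
| 1.2 | 0.7 | 0.84 | 0.966 | 83.2% | 0.114 |
| 1.4 | 0.7 | 0.98 | 1.00 | 82.0% | 0.116 |

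**5. Effect of chance imbalance on a contrast.** With equal SDs, SD₀ = 0.35/√(2(1 − r)). A one-standard-error baseline difference between two arms of 70 moves the change-score contrast by (1 − r) × SD₀ × √(2/70) = 0.35 × √((1 − r)/2) × 0.169. This is 0.035, 0.030 and 0.023 at r = 0.3, 0.5 and 0.7, or 21%, 17% and 13% of the 0.17 target. At r = 0.9 it is 0.013, or 8%.

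**The case against.** The strongest reply is that nothing here is wrong. A change-score comparison is valid under randomisation, the stated sample size meets its power and width targets, and the ANCOVA is already pre-specified for the primary and secondary endpoints. That stands, and it keeps the point modest. What remains is that the less efficient of two planned analyses governs the efficacy conclusion and the dose choice.

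A reader might infer more than the documents support:

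- **That the primary analysis is wholly unadjusted, or uses SNAP only conditionally.** Section 6.1.5 always builds the intervals by SNAP stratum. Only combining them depends on there being no interaction.
- **That the result is biased by regression to the mean.** Eligibility uses the diary average between Visits 2 and 3, while the baseline week begins at Visit 3. Any remaining regression affects the randomised arms equally in expectation.
- **That a known number of subjects is being wasted.** The gain depends on r and k, which the protocol does not give. Weekly means of about five prompts a day reduce measurement noise, so a high r is plausible. Entry requires a mean of at least 0.74 on a scale that ends at 1.77. That may narrow the baseline spread and make k greater than 1. Both reduce the gain.
- **That two analyses of one endpoint leave the answer unclear.** The protocol says which is primary.
- **That centre must be in the model.** Section 3.3.2 says "Subjects will be stratified by center and SNAP status", but no gain from a centre term can be calculated from the documents. At 355/30, about 12 subjects per centre, the term would be thinly estimated.

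The interim resizing in Section 6.1.8 does protect the interval width, but it does so by adding subjects, up to 500 randomised. Adjustment adds none.

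**Conclusion.** The point holds as a free improvement in efficiency and in the stability of the dose ranking. It is not a finding of error, bias or inadequate power. With equal SDs and r from 0.3 to 0.9, the variance falls by 35% to 5%. Power at 70 per group then exceeds the planned 81–82%, by about 13 percentage points at r = 0.3 and about 2 at r = 0.9. Both the correlation and the SD ratio are assumptions, and the gain reaches zero when the slope is near 1. The direction is secure because the adjustment costs about one degree of freedom; the size cannot be fixed from the protocol.

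**What to change.** Before unblinding, and before the interim analysis if its rules are to follow the same model:

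1. In Section 6.1.5 and the synopsis, make the primary analysis an ANCOVA with dose, Week 0 Gracely mean and SNAP stratum. Keep the planned check of treatment-by-SNAP interaction.
2. Take the 95% intervals and the dose-selection lower bounds from this model. Keep the change-score interval without the baseline covariate as supportive.
3. In Section 6.1.8, align the SD check, the predicted intervals and the 0.24 width target with the adjusted model. State which SD is meant, because 0.35 is the SD of the change and not a residual SD.
4. In Section 6.3, state that the sample size from the change-score SD of 0.35 is conservative for the adjusted analysis.
5. A centre term (random, or with small centres pooled) is optional.

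The cost is wording in four places. No data, visits or subjects are added, since Week 0 scores are already part of the endpoint and the ANCOVA is already planned.

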### 3.1.2. Stratification

Study subjects will be stratified into 2 categories by the sural nerve action potentials determined at baseline by standardized antidromic sural nerve action potential amplitude measurements (0-4.0 μV and >4.0 μV).

A stratified randomization schema will be included to balance the distribution of SNAP positive and SNAP negative subjects at approximately 1:1 to avoid a mal-distribution with an excessive number of SNAP negative subjects who might have reduced treatment response.

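### The combined primary interval for each dose exists only if no treatment-by-SNAP interaction is declared, so the primary estimate depends on the data and is undefined if one is

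*Protocol*

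**What the plan says.** Protocol 6.1.5 plans 95% intervals for each dose against placebo, first within each SNAP stratum. The overall interval follows on a condition: "If there is no interaction between treatment efficacy and SNAP, the two intervals will be combined across the strata". Section 6.1 puts the same condition on the data as a whole, which are to be "combined in the final analysis if there is no interaction between treatment effects and SNAP status". The recommended dose, if safety is similar, is the one whose interval has the highest lower limit (6.1.5).

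Other places carry no such condition. The synopsis, under statistical methods, plans the primary-endpoint intervals for each dose without mentioning SNAP. Section 6.1 also says that each dose will be compared with placebo and given a 95% interval.

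The sample size section (6.3) is written for the whole group: "This study is designed to detect a minimum treatment difference of 0.17 between any dose group and placebo", and "In order to have at least 80% power to detect this difference and a significance level of 0.05 (2-sided), 70 evaluable subjects" in each of the 4 mg, 8 mg, 16 mg and placebo groups. It gives no power or precision for a stratum or for the interaction.

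On the stratum sizes, 3.1.2 says that the stratified randomization is to "balance the distribution of SNAP positive and SNAP negative subjects at approximately 1:1".

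**The concern.** The trial's own data decide whether the planned primary comparison is produced. If an interaction is declared, 6.1.5 leaves two stratum intervals per dose. It does not say which answers the primary question, or which lower limit enters the dose ranking. The sample size assumes that the combined comparison is always available.

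The condition also asks for something the trial cannot show. A test with little power that fails to reject is not evidence that the effect is the same in both strata. The strata would therefore usually be combined for want of evidence, and occasionally separated by chance.

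A smaller point concerns the stratum sizes. Section 3.3.2 describes allocation of treatments within centre and SNAP group. That balances treatments inside a stratum. It does not set the ratio of SNAP-positive to SNAP-negative subjects, and no enrolment cap is stated.

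**Working it through.** **Inputs.** From section 6.3: difference 0.17, SD of change 0.35, 70 evaluable per group, two-sided 0.05, at least 80% power. From 3.1.2: strata of about equal size, hence about 35 per group per stratum. The level for an interaction test is not stated; 0.05 is inferred from the general rule in 6.1, "The significance for all statistical tests will be reported at the p=0.05 level, and all tests will be 2-sided".

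**1. The plan's own figure, 70 against 70.**
- SE = 0.35 × √(2/70) = 0.0592.
- Half-width = 1.96 × 0.0592 = 0.116, which the protocol rounds to 0.12.
- Power = Φ(0.17/0.0592 − 1.96) = Φ(0.91) = 82.0%; by t-test 81.4%. The stated figure reproduces.

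**2. One stratum, 35 against 35.**
- SE = 0.35 × √(2/35) = 0.0837.
- Half-width = 1.96 × 0.0837 = 0.164.
- Power for 0.17 = Φ(2.03 − 1.96) = 52.9%; by t-test 51.7%.
- The result depends on the split. Assumed splits of 40:60 and 30:70 give 44% and 60%, and 35% and 67%, in the smaller and larger stratum (normal approximation).

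**3. Interaction test for one dose.**
- SE of the difference between the stratum effects = 0.35 × √(4/35) = 0.118.
- Power for a stratum difference of 0.17 at 0.05 = Φ(1.44 − 1.96) + Φ(−1.44 − 1.96) = 30%. At levels of 0.10 and 0.20 it is 42% and about 57%.
- Difference detectable with 80% power = 0.118 × (1.96 + 0.84) = 0.33, about twice the design effect.

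**4. What the condition costs when there is no true interaction.**
- A single test at 0.05 splits the analysis 5% of the time.
- With equal strata, the average and the difference of the two stratum estimates are independent. The chance of a significant combined result that is also not split is therefore 0.82 × 0.95 = 78%, against 82% without the condition.
- If each of three doses were tested separately at 0.05 (an assumption), at least one would be split in about 12.5% of trials. This is a simulated figure that allows for the shared placebo group.

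**5. The proposed primary estimate.** Weight each stratum by its precision, with treatments balanced within strata and a common SD.
- The variance is 2 × 0.35²/70 whatever the SNAP split, so power stays at 81-82% and the half-width at 0.116.
- If the effect is 0.17 in SNAP-positive and 0 in SNAP-negative subjects at 1:1, the average is 0.085. Its power is Φ(0.085/0.0592 − 1.96) = Φ(1.44 − 1.96), about 30%, against about 52% within the SNAP-positive stratum.

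**The case against.** SNAP is not an arbitrary subgroup. The introduction reports, from a post-hoc analysis of the diabetic neuropathy trial, a weaker effect in subjects without a recordable SNAP. The dose selection section stratifies in order to evaluate the sural nerve hypothesis. If that hypothesis is true, an unconditional combined estimate averages an effect with none, and step 5 shows that it has less power than the SNAP-positive stratum. This stands as a real cost of the fix. It is limited because the stratum intervals are reported either way.

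A test and its level are often left to a statistical analysis plan, which is not shown. That also stands for the criterion. It does not remove the point, because the protocol itself makes the combined interval conditional, and an analysis plan that combined the strata unconditionally would contradict it.

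Some stronger readings are tempting but not supported:
- **That 80% power is replaced by two comparisons at 52%.** This describes what follows a split. With a homogeneous effect a split occurs about 5% of the time per test.
- **That one dose would be judged on 70 per group and another on 35, or that 12.5% of trials would be affected.** Both need separate tests for each dose, which the protocol does not specify. The wording in 6.1 fits a single overall test equally well.
- **That no overall result would exist for a split dose.** The synopsis and 6.1 promise dose-versus-placebo intervals without condition, and 6.1.5 also plans a baseline-adjusted ANCOVA. The text conflicts about which result leads; it does not clearly abolish the overall one.
- **That the false-positive rate rises to about 8% per dose.** This counts either stratum interval as a success after a split, a rule the protocol never states.

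**Conclusion.** The point holds and should be fixed, but it does not invalidate the design. The protocol lets an unspecified interaction judgement decide whether the powered comparison is produced, leaves the primary estimate and the ranking interval undefined if an interaction is declared, and contradicts its own unconditional statements.

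The contrast between 81-82% and about 52% power assumes a true effect of 0.17 in the stratum concerned, SD 0.35 and equal strata. The 30% figure assumes a test at 0.05; more lenient levels raise it but also split more often by chance. The average loss of power is modest, about 82% to 78% when the effect is homogeneous. The harm lies in the data-dependent choice of estimate.

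The 1:1 statement in 3.1.2 is a secondary correction. The figure of 35 per stratum takes that statement at face value, and steps 2 and 5 show how far departures from it matter.

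**What to change.** - **6.1 and 6.1.5:** delete the no-interaction condition. Make the SNAP-stratified combined difference from placebo the primary estimate for each dose and the basis of the dose ranking.
- **6.1.5:** report the stratum intervals and the treatment-by-SNAP interaction as pre-specified supportive analyses addressing the sural nerve hypothesis.
- **Link to 6.1.8:** the interim analysis may end SNAP-negative enrolment. State how the combined estimate is then formed and weighted, since the stratum sizes, and so the population it describes, would change.
- **3.1.2:** say that stratified blocks balance treatments within each SNAP stratum, and that the positive-to-negative ratio is as enrolled.

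The cost is wording only, to be settled before unblinding, with no extra subjects. The price is that the primary estimate is an average if SNAP modifies the effect, with about 30% power in the case of 0.17 against 0. The supportive stratum results would still show such a pattern.
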